### 6.1.3. Blood Glucose Management

In this study, after the patient returns to the ward immediately post-surgery, the sub-investigator will attach the FreeStyle Libre Pro to the outer upper arm of the patient and begin continuous glucose monitoring (CGM). The sub-investigator will remove the FreeStyle Libre Pro from the patient on postoperative day 9. In addition, from the time the patient returns to the ward, blood glucose will be routinely measured 4 times a day using either blood gas analysis or the Dexter system.

Rescue treatments for hyperglycemia and hypoglycemia will be managed based on the blood glucose values obtained from the routine measurements via blood gas analysis or the Dexter system. Blood glucose information obtained from the FreeStyle Libre Pro will not be used as a reference for determining whether to perform rescue treatments for hyperglycemia or hypoglycemia.

Rescue treatments for hyperglycemia and hypoglycemia will be conducted as described below. However, rescue treatment for blood glucose levels between 201-299 mg/dL will not be permitted until the second postoperative day.

Criteria for rescue treatment for postoperative hyperglycemia and hypoglycemia

| Blood glucose (mg/dL) | | season | Fast-acting insulin | 50% Dextrose |
| --- | --- | --- | --- | --- |
| Hyperglycemia | 201 or more ~ 249 or less | Up to postoperative day 2 | None | - |
|  |  | From the 3rd postoperative day onwards | 2 Units | - |
|  | 250 or more ~ 299 or less | Up to postoperative day 2 | None | - |
|  |  | From the 3rd postoperative day onwards | 4 Units | - |
|  | 300 or more ~ 349 or less | Postoperative day 1 and beyond | 6 Units | - |
|  | 350 or more ~ 399 or less | Postoperative day 1 and beyond | 8 Units | - |
|  | 400 or more | Postoperative day 1 and beyond | 10 Units | - |
| hypoglycemia | 69 or less | Postoperative day 1 and beyond | - | 20mL |

<Rationale for rescue treatment for hyperglycemia and hypoglycemia>

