## 6.2. Criteria for Protocol Treatment Completion, Discontinuation, or Modification

### 6.2.1. Definition of Protocol Treatment Completion

The initiation of protocol treatment is defined as the application of the FreeStyle Libre Pro. The protocol treatment is considered complete when the administration of Meiji Main, Glucerna®-REX, or any other nutritional formula is finished and the FreeStyle Libre Pro is removed.

If Meiji Main, Glucerna®-REX, or any other nutritional formula is administered up to postoperative day 8 and the FreeStyle Libre Pro remains attached until postoperative day 9, the protocol treatment is deemed complete

.

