### 6.2.2. Criteria for Protocol Treatment Discontinuation

Protocol treatment will be discontinued in any of the following situations. The date of protocol treatment discontinuation will be defined as the date of death in the event of death or the date on which the attending physician determines that protocol treatment should be discontinued for other reasons.

When it becomes difficult to continue the study due to adverse events.

1. If the patient offers to discontinue protocol treatment.
2. Death during protocol treatment
3. When it is determined that discontinuation is necessary at the discretion of the principal investigator or co-investigator.
4. During the ICU period (within 4 days after surgery), the sensor is removed and the missing data is revealed.
5. By the second postoperative day, hyperglycemia (300 mg/dL or more) requiring insulin administration.
6. By the second postoperative day, the patient has a hypoglycemic condition (69 mg/dL or less) that requires sugar administration.
7. Skin troubles attributed to the FreeStyle Libre Pro sensor adhesive.
8. The need arises to remove the seal on the FreeStyle Libre Pro sensor for an MRI examination.
9. In addition, if serious deviations from the protocol are discovered, such as protocol violations, post-registration surgical procedures, or changes in treatment policies.

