**・All Registered Cases**
All patients who have been registered are referred to as "All Registered Cases."

- **Full Analysis Set (FAS)**
   The group derived from the "All Registered Cases" after excluding patients with significant eligibility criteria violations, patients who violated exclusion criteria, patients who did not receive any protocol treatment, patients with no efficacy-related data, and patients who withdrew consent and refused to allow the use of any data. This group is defined as "FAS."
- **PPS (Per Protocol Set)**
   The group derived from the "FAS" after excluding patients who discontinued protocol treatment by the second postoperative day or had significant protocol violations is defined as "PPS."
- **All Treated Cases**
   Patients who received part or all of the protocol treatment are referred to as "All Treated Cases".

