## 11.2. Handling of Missing Data

As a general rule, missing data will not be imputed. However, if necessary, analyses with imputed missing data will be conducted as sensitivity analyses. Details on the handling of missing data will be described in the statistical analysis plan. If the sensor detaches for any reason during the ICU stay, resulting in missing data, a sensitivity analysis will also be performed on cases where the data collected from the time the sensor was attached until the time it detached covers 70% or more (6.3 days or more) of the planned measurement days, based on the previously reported recommendations [8, 12].

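### The per-protocol sensitivity analysis drops patients for glucose values that count against them in the primary endpoint, and the protocol does not say whether CGM continues once they stop

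*Protocol*

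**What the plan says.** Section 6.2.2 is mandatory: "Protocol treatment will be discontinued in any of the following situations". Two of the listed situations are glucose events: "By the second postoperative day, hyperglycemia (300 mg/dL or more) requiring insulin administration" and "By the second postoperative day, the patient has a hypoglycemic condition (69 mg/dL or less) that requires sugar administration".

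Section 6.1.3 lists the same events, in the same period, as rescue treatment, for example "300 or more ~ 349 or less | Postoperative day 1 and beyond | 6 Units". Section 6.3.1 describes that rescue as permitted, and secondary endpoint 12 counts interventions at 300 mg/dL or more. None of these places says that rescue ends protocol treatment.

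Section 6.2.1 ties protocol treatment to the sensor. At the start, "The initiation of protocol treatment is defined as the application of the FreeStyle Libre Pro". Treatment is complete when the assigned formula or "any other nutritional formula is finished and the FreeStyle Libre Pro is removed".

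Section 11.1 puts the efficacy analyses, including the main one, in the FAS. Its list of FAS exclusions does not contain discontinuation. The PPS, which serves as the sensitivity analysis, is formed by "excluding patients who discontinued protocol treatment by the second postoperative day or had significant protocol violations". Section 11.2 adds: "As a general rule, missing data will not be imputed". It allows imputed analyses as sensitivity analyses and leaves details to the SAP. Section 11.3 defines the primary endpoint as the proportion of 48 hours within 70-180 mg/dL.

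**The concern.** Both glucose triggers lie outside the 70-180 mg/dL target range and fall in the period over which the primary endpoint is measured. A patient who meets one has, for that reason, tended toward a low TIR. Removing such patients raises the mean TIR of the arm that loses them. The trial's hypothesis is that the study formula suppresses hyperglycaemia. If that is true, the 300 mg/dL trigger should fire more often in the control arm, and the PPS difference will understate the effect. A sensitivity analysis that moves for this reason says little about the robustness of the main result.

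Two features add to this. Section 6.1.3 withholds insulin at 201-299 mg/dL until after POD2, whereas section 2.2.2 describes usual care as treating from 201, so more patients may reach 300 than under usual care. Also, the trial is open-label, and section 6.2.2 dates discontinuation by the attending physician's decision. Whether a stop counts as being by POD2 therefore rests partly on an unblinded judgement.

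A second exposure is data capture. If staff take discontinuation to mean that the sensor comes off, the rest of the 48 hours and the POD3-8 recordings are lost in the most dysglycaemic patients. An SAP can say how to analyse missing CGM data; it cannot recover recordings that were never made.

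**Working it through.** **1. The plan's own figure.** Section 11.6 gives 48 analysed patients (taken as 24 per arm), SD 8.5% and a precision of about ±5%. Reading 8.5% as the per-patient SD in each arm:

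- half-width = t(0.975, 46) × 8.5 × √(2/24) = 2.013 × 2.454 = 4.94 points (4.81 with the normal quantile).

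The stated ±5% is reproduced, so 8.5% is the SD to use below.

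**2. Shift in an arm mean when low-TIR patients are excluded.** The protocol gives no rate for either trigger, so the rates here are assumptions. Let q be the share excluded and ρ the strength of the link between triggering and low TIR (ρ = 1 means exactly the lowest-TIR patients trigger). Under a normal model:

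- rise in arm mean = ρ × 8.5 × φ(z_q)/(1 − q), where z_q is the q-quantile of the standard normal distribution.

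At ρ = 1:

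- q = 2%: 8.5 × 0.0484/0.98 = 0.42
- q = 5%: 8.5 × 0.1031/0.95 = 0.92
- q = 10%: 8.5 × 0.1755/0.90 = 1.66
- q = 20%: 8.5 × 0.2800/0.80 = 2.97

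**3. Shift in the PPS difference (intervention minus control).**

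| Control excluded | Intervention excluded | ρ = 0.5 | ρ = 1.0 |
| --- | --- | --- | --- |
| 10% | 2% | −0.62 | −1.24 |
| 20% | 5% | −1.03 | −2.05 |
| 10% | 10% | 0 | 0 |

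With equal exclusion both arm means rise by 0.83 to 1.66 points, but the difference does not move. Against the 4.94-point half-width, the non-zero shifts are 0.62/4.94 = 13% to 2.05/4.94 = 41%. Both the shift and the half-width scale with the SD, so these ratios do not depend on 8.5% being right.

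**4. Precision of the PPS.** With SD 8.5%, losing 4 of 24 control patients gives t(0.975, 42) × 8.5 × √(1/24 + 1/20) = 5.19. Losing 6 of 24 gives t(0.975, 40) × 8.5 × √(1/24 + 1/18) = 5.36.

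**5. Does CGM stop at discontinuation?** Set side by side:

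- Section 6.2.1 makes sensor application the start of protocol treatment and sensor removal part of its completion. It does not cover discontinuation.
- In section 6.2.2, three criteria mention the sensor (detachment with data loss, skin trouble, MRI). The two glucose criteria do not.
- Sections 6.1.3 and 8.6 schedule sensor removal on POD9 and make no separate provision for patients who have stopped.
- Section 13.2.3 says follow-up continues after a patient refuses further treatment, but mentions neither CGM nor a glucose-triggered stop.
- The 70% sensitivity analysis in section 11.2 concerns sensor detachment in the ICU, not this case.

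The text supports either reading and settles neither.

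**The case against.** The main analysis is in the FAS, which keeps a discontinued patient who has any efficacy data. A PPS ordinarily excludes early discontinuations, and the selection this brings is why it is only a sensitivity set here. The trial estimates a difference and generates hypotheses, with p-values given for reference. All of this stands, and it limits the certain harm to the PPS.

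Rescue and discontinuation can also both apply: the hyperglycaemia criterion presupposes that insulin was given, and an event counted under endpoint 12 may also end treatment. So the sections are unreconciled rather than flatly incompatible.

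Three stronger readings are tempting and are not supported:

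- *That discontinuation ends sensor wear, so the primary analysis loses patients.* No section says the sensor comes off under the glucose criteria, and the FAS has no exclusion for discontinuation.
- *That lost data are simply never imputed.* Section 11.2 allows imputed sensitivity analyses, and the scoring of a partial 48 hours may be settled in the SAP, which is not shown.
- *That the PPS could lose close to half the effect.* Suppose 16% of control and 8% of intervention patients trigger with a mean TIR of 15%, and the others average 70% and 75%. The full difference is (0.08 × 15 + 0.92 × 75) − (0.16 × 15 + 0.84 × 70) = 70.2 − 61.2 = 9.0, against 5.0 in the PPS. But that mixture alone implies SDs of √(0.16 × 0.84) × 55 = 20.2 and √(0.08 × 0.92) × 60 = 16.3, against the planned 8.5%. With SD 8.5% and 16% excluded, the largest possible gap is 8.5/√0.1344 = 23.2 points, not 55. The trigger is also one of four routine readings a day, which does not imply so low a TIR.

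Finally, the low-glucose trigger could fire more often in the intervention arm and push the PPS difference the other way. The direction is therefore conditional.

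**Conclusion.** As written, the PPS sensitivity analysis excludes patients because of the outcome being measured. That follows from sections 6.2.2, 11.1 and 11.3 without any assumption. Its size is not known. Under the assumed unequal exclusions, a normal model, ρ from 0.5 to 1.0 and the planned SD, the PPS difference moves toward zero by about 0.6 to 2.1 points, with no net shift if the arms are affected equally.

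The FAS main analysis and the POD1-8 TIR, TAR and AUC are at risk only if CGM stops at discontinuation. The protocol permits that reading without stating it. This second part needs settling in the protocol itself, because any loss would be irreversible.

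**What to change.** 1. In sections 6.2.2 and 8, state that after discontinuation under the two glucose criteria the sensor stays on and CGM is collected as scheduled where possible, at least through POD2.
2. In sections 11.1 to 11.3, state that the FAS analyses use all recorded CGM data regardless of rescue or discontinuation.
3. In section 11.1, do not exclude from the PPS on glucose-triggered discontinuation alone, or report the PPS with and without these patients.
4. Reconcile sections 6.1.3 and 6.3.1 with 6.2.2 on whether these events are in-protocol rescue, discontinuation or both. This is for the investigators to settle; no clinical rule is proposed here.

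The cost is protocol and SAP wording, plus sensor-days that are already planned on a sensor already in place. The downside is that the PPS will include some patients who received rescue or stopped the assigned formula early, so it becomes a less strict picture of adherence. Reporting it both ways keeps that visible.

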### 6.2.3. Change Criteria for Protocol Treatment

Adverse events related to the enteral formula (see Section 7.1.1) may necessitate changes to an alternative formula (selected from existing nutritional formulas deemed appropriate by the principal investigator or sub-investigator) or a reduction in the dosage of the enteral formula for both the control and intervention groups. If Grade 3 or higher symptoms (as defined by CTCAE ver. 5.0) are observed, both the control and intervention groups will either switch to an alternative nutritional formula, as determined appropriate by the principal investigator or sub-investigator or reduce the dosage of the protocol formula by 50% or more compared to the previous day, without changing the protocol formula itself.

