**Secondary endpoints**:

1. Incidence rate of infectious complications during hospitalization

2. Incidence rate of infectious complications within 30 days postoperatively

3. Incidence rate of all complications during hospitalization

4. Incidence rate of adverse events

5. Average value of Time Above Range (TAR) during the entire measurement period

(postoperative days 1-8) measured by CGM

6. Daily TAR values measured by CGM up to postoperative day 8

7. Average value of Area Under the Curve (AUC) during the entire measurement period

(postoperative days 1-8) measured by CGM

8. Daily AUC values measured by CGM up to postoperative day 8

9. Average value of Time in Range (TIR) during the entire measurement period (postoperative days 1-8) measured by CGM

10. Daily TIR values measured by CGM up to postoperative day 8

11. Rate of change in nutritional indicators during hospitalization compared to the time of admission (serum albumin, prealbumin, and total protein levels)

12. Number of cases requiring blood glucose control intervention for hyperglycemia (≥ 300 mg/dL)

13. Number of cases requiring changes to enteral nutrition formulas from postoperative day 3 onwards

14. Number of cases requiring a reduction of more than 50% in enteral nutrition from the previous day after postoperative day 3

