## 6.3. Combined treatment and supportive treatment

### 6.3.1. Acceptable combination and supportive care for hyperglycemia and hypoglycemia

Rescue treatments for hyperglycemia and hypoglycemia (as outlined in Section 6.1.3 Blood Glucose Management) are the only interventions permitted.

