# 7. Anticipated Adverse Events

## 7.1. Expected Adverse Events and Defects

### 7.1.1. Adverse Events Associated with Enteral Nutrition (Meiji Main and Glucerna-REX ®)

1. Aspiration
2. diarrhea
3. constipation
4. Bloating
5. stomach ache
6. nausea
7. vomiting
8. Small bowel obstruction
9. Hyperglycemia
10. hypoglycemia

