## 8.2. Evaluation items on the day of surgery

1. Surgery Information
2. Allocation
3. FreeStyle Libre Pro attachement
4. 24-hour continuous glucose monitoring
5. Confirmation of Survival

## 8.3. Evaluation Items on Postoperative Day 1

1. Conformation of FreeStyle Libre Pro Continues
2. 24-hour continuous glucose monitoring
3. Blood glucose measurement 4 times a day with blood gas
4. Continuous administration of 400 mL of enteral nutrition (Meiji Main and Glucerna®-REX)
5. If necessary, the rescue of insulin for hyperglycemia and hypoglycemia
6. Presence or absence of postoperative infectious complications
7. Presence or absence of other complications
8. Adverse events
9. Confirmation of survival or death

## 8.4. Evaluation Items on Postoperative Days 2 to 3

1. Conformation of FreeStyle Libre Pro Continues
2. 24-hour continuous glucose monitoring
3. Blood glucose measurement 4 times a day with blood gas
4. Continuous administration of enteral nutrition (Meiji Main and Glucerna-REX ®) (postoperative day 2; 800 mL, postoperative day 3: 1200 mL)
5. If necessary, the rescue of insulin for hyperglycemia and hypoglycemia
6. Presence or absence of postoperative infectious complications
7. Presence or absence of other complications
8. Adverse events
9. Confirmation of survival or death

## 8.5. Evaluation Items on Postoperative Days 4 to 8

1. Conformation of FreeStyle Libre Pro Continues
2. 24-hour continuous glucose monitoring
3. Blood glucose measurement 4 times a day with dexter
4. Continuous administration of enteral nutrition (Meiji Main and Glucerna-REX ®) (postoperatively 4 days or later; 1600 mL)

Dosage may be changed or enteral nutrition may be changed depending on the patient's condition (e.g., adverse events) (see 6.2.3.)

1. If necessary, the rescue of insulin for hyperglycemia and hypoglycemia
2. Presence or absence of postoperative infectious complications
3. Presence or absence of other complications
4. Adverse events
5. Confirmation of survival or death

## 8.6. Evaluation Items on Postoperative Day 9

1. Remove the FreeStyle Libre Pro. (Postoperative 1~Collection of blood glucose data on day 8)
2. Enteral nutrition: Change of administration to Heinegel (change timing can be changed depending on the patient's condition)

However, if Meiji Main and Glucerna-REX ® are still administered after the 9th postoperative day, until the end of administration

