## 11.5. Sub-secondary evaluation (safety)

For the following items, calculate the frequency, percentage, and corresponding 95% confidence interval for each group. The 95% confidence intervals should be calculated using Clopper & Pearson's exact confidence interval method. If necessary, perform a chi-squared test to compute the p-values for comparisons between the two groups.

For adverse events, calculate the number of cases, number of occurrences, proportion of cases, and their 95% confidence intervals using Clopper & Pearson's exact method. The analysis should also include a breakdown by grade and causal relationship. Additionally, create a comprehensive list of all adverse events.

- Incidence rate of infectious complications during the hospitalization period
- Incidence rate of infectious complications within 30 days postoperatively
- Incidence rate of all complications during the hospitalization period
- Incidence rate of adverse events
- Number of cases requiring glycemic control intervention for hyperglycemia (≥ 300 mg/dL)
- Number of cases in which enteral nutrition was modified after postoperative Day 3
- Number of cases requiring a reduction of more than 50% of enteral nutrition compared to the previous day after postoperative Day 3

For the following items, calculate the median and interquartile range (IQR) for each group at all measurement points. Also, calculate the median and IQR for changes from baseline values (pre-registration measurements). If necessary, also calculate the mean and standard deviation, as well as p-values using the Wilcoxon test.

- Nutritional indicators during the hospitalization period (serum albumin levels, prealbumin levels, and total protein levels)

)

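### Endpoint 14 does not count the exact halving of the feed that 6.2.3 prescribes, and 6.2.3 leaves unclear whether a glucose event alone may change the formula

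*Protocol*

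**What the plan says.** **The rule for changing the feed.** Section 6.2.3 applies to both arms. "Adverse events related to the enteral formula (see Section 7.1.1) may necessitate changes to an alternative formula" or a lower dose of the same formula. At CTCAE Grade 3 or higher the choice becomes mandatory: switch to another formula, or keep the formula and "reduce the dosage of the protocol formula by 50% or more compared to the previous day".

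**The endpoint that counts reductions.** Endpoint 14 is listed in sections 0.2, 1 and 10.1 as "Number of cases requiring a reduction of more than 50% in enteral nutrition from the previous day after postoperative day 3". Its analysis entry in 11.5 has the same threshold: "Number of cases requiring a reduction of more than 50% of enteral nutrition compared to the previous day after postoperative Day 3".

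**What can trigger a change.** The list in 7.1.1, to which 6.2.3 points, has "Hyperglycemia" as item 9 and hypoglycemia as item 10. Section 6.2.3 excepts neither. Section 6.3.1 says of these two conditions that the rescue treatments of 6.1.3 "are the only interventions permitted". Those treatments are insulin and dextrose. Section 8.5 (days 4 to 8) repeats the permission, citing 6.2.3: "Dosage may be changed or enteral nutrition may be changed depending on" the patient's condition.

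**The concern.** Endpoint 14 reads as the count of patients whose feed had to be cut substantially. A reader will expect it to cover the cuts that 6.2.3 prescribes, but the rule includes exactly 50% and the endpoint excludes it. Halving is the simplest way to comply with 6.2.3 and the smallest cut that does so. If clinicians choose it, the tolerability count leaves out patients whose feed was reduced under the protocol's own rule. If one arm is halved more often than the other, the comparison between arms is affected too.

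The second matter is the trigger. The trial asks whether the formula changes glucose. If a glucose event can change the formula or its volume, exposure partly follows outcome, and the later CGM summaries partly describe that feedback.

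**Working it through.** The plan attaches no expected figure to endpoint 14, so there is none to reproduce. The check compares the two thresholds at the scheduled doses of section 6.1.2 (400, 800 and 1200 mL on days 1 to 3, then 1600 mL on days 4 to 8).

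**Step 1: exact halving.** Reduction = (previous day − new dose) / previous day.

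| Day of cut | Previous day (mL) | New dose (mL) | Reduction | 6.2.3 (50% or more) | Endpoint 14 (more than 50%) |
|---|---|---|---|---|---|
| 4 | 1200 | 600 | 600/1200 = 50.0% | satisfied | not counted |
| 5 to 8 | 1600 | 800 | 800/1600 = 50.0% | satisfied | not counted |

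If day 3 is taken to belong to the endpoint's window, 800 to 400 mL gives the same result.

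**Step 2: which part of the rule is lost.** Formula switches are counted separately by endpoint 13, from day 3. The gap concerns only the dose-reduction option, and within it only cuts of exactly 50%.

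**Step 3: size.** The document does not say how often feeds are cut or how many cuts are exact halvings. The share of prescribed cuts missed can lie anywhere from none to all. With 25 patients per arm, each patient missed lowers the reported proportion by 1/25 = 4 percentage points.

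**Step 4: where a glucose trigger could act.**

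- *To day 2.* Section 6.1.3 states that "rescue treatment for blood glucose levels between 201-299 mg/dL will not be permitted until the second postoperative day". Items 5 and 6 of 6.2.2 discontinue protocol treatment when values of 300 mg/dL or more need insulin, or values of 69 mg/dL or less need sugar. The primary endpoint, TIR to day 2, is therefore largely protected. It is not fully protected, because 6.2.3 carries no day limit.
- *Days 3 to 8.* These are 6 of the 8 days averaged in the secondary TIR, TAR and AUC endpoints (75%). By volume they are (1200 + 5 × 1600) / (400 + 800 + 1200 + 5 × 1600) = 9,200/10,400 = 88.5% of the planned feed.

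**Step 5: what one halved day removes.** On days 5 to 8, 800 mL is withheld. Using the composition table in 2.3.2:

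- Total carbohydrate (15 and 9.7 g per 100 mL): 120 g in a control patient, 77.6 g in an intervention patient.
- Without fibre (13.2 and 8.8 g per 100 mL): 105.6 g and 70.4 g.

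These are amounts of feed. The document offers no way to convert them into TIR, and it gives neither the CTCAE glucose cut-offs nor a rate of such events.

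**The case against.** **On endpoint 14.** The mismatch may be a slip in wording. The protocol is loose about boundaries elsewhere: the table in 6.1.3 acts at 69 or less and 300 or more, while the rationale below it speaks of falling below 69 and exceeding 300. The endpoint is one descriptive count in a hypothesis-generating trial (2.6). If delivered rather than prescribed volumes are used, few will be exactly half. All of this limits the importance. None of it makes the rule and the count agree, and the stricter threshold is written the same way in all four places.

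**On the glucose trigger.** A reader might infer that 6.2.3 and 6.3.1 contradict each other. The document does not establish that. Section 6.3.1 sits under concomitant and supportive treatment, whereas 6.2.3 governs modification of the study feed. On that reading one limits added therapy, the other the formula, and both can stand. The trigger may also be narrow: 6.2.3 speaks of events related to the formula, and 7.4 calls an event related only if other factors cannot explain it. The protocol itself names surgical stress (2.1) and prophylactic steroid (rationale for exclusion criterion 7) as influences on postoperative glucose. Insulin from 201 mg/dL is already allowed in both arms from day 3, so the later CGM endpoints include glucose-driven treatment in any case. Feed changes for adverse events are deliberate: 6.2.1 counts a patient on another formula as complete.

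These points stand, and they reduce this part to a clarification. What remains is that neither section refers to the other, so a clinician with a hyperglycemic patient on day 5 cannot tell whether a feed change is open.

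**Conclusion.** The endpoint 14 mismatch holds as written. A cut of exactly 50% follows 6.2.3 and is left out of the count. Its numerical effect is unknown, at 4 percentage points per missed patient with 25 in an arm.

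The glucose trigger is an ambiguity worth closing. It bears mainly on the secondary CGM endpoints over days 3 to 8.

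Three stronger readings are not supported:

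- That the primary endpoint is compromised. Sections 6.1.3 and 6.2.2 largely protect it.
- That the protocol orders the feed to be halved for hypoglycemia. A switch is the stated alternative, and the event must first be attributed to the feed.
- That the secondary TIR results would shift by some stated amount. Any such figure would need event rates and a link from carbohydrate to TIR, and the document gives neither.

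The sample size and the primary analysis are unaffected.

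**What to change.** **Main change.** In sections 0.2, 1, 10.1 and 11.5, define endpoint 14 as a reduction of 50% or more from the previous day. Change the endpoint and not 6.2.3: raising the rule to more than 50% would alter patient care only to suit a count.

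**Clarification.** Add one sentence to 6.2.3: *Hyperglycemia and hypoglycemia are managed under 6.1.3 and 6.2.2 and do not by themselves trigger a change of formula or dose.*

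**Cost.** The changes are a few words in four places and one added sentence, with no extra patients, visits or procedures. The real cost of the clarification is less freedom to adjust the feed for glucose. When rescue is not enough, the remaining route is to discontinue protocol treatment at the investigator's discretion under 6.2.2 item 3, which is a larger step than a dose cut. If the sponsor prefers to keep feed adjustment available, it should say so in 6.2.3 and 6.3.1, and accept that the later CGM endpoints then include it.
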